#### The safety profile of supplements

Marangell et al. studied the impact of O3FA supplementation (2,960 mg/day) on the prevention of postpartum depression. Adverse events reported were mild. Four participants reported a “fishy” aftertaste, one reported mild dyspepsia, and one reported increased stool frequency with loose stools. There were no withdrawals due to adverse events (32). Similarly, Su et al. completed an RCT with 24 participants. No withdrawal of participants due to adverse events was reported. In total, 12/18 participants in the placebo group and 10/18 in the O3FA group did not report any adverse events. Events reported included insomnia (two in the placebo group and three in the O3FA group), nausea (four in the placebo group and six in the O3FA group), and diarrhea (two in the placebo group and one in the O3FA group). The authors noted that most events were mild, with the exception of significant nausea for one participant in the placebo group, which led to the termination of treatment. The authors reported no effects on biological parameters, including abnormal bleeding time or liver function. All newborns were in normal general health at birth (33). Furthermore, Mattes et al. studied O3FA supplementation (3.7 g/day) in 83 pregnant women in the prevention of maternal depression. The authors documented no adverse events (34).

The 2020 meta-analyses by Zhang et al. examined the efficacy and safety of EPA and DHA monotherapy in the treatment of perinatal depression in women with a clinical diagnosis of MDD or symptomatic depression in pregnancy and/or postpartum. Only randomized double/triple-blinded placebo-controlled trials were included in this study (*N* = 8) (35). A total of 638 pregnant women were administered 1–6 g/day a day. The safety of doses of 1–6 g/day was demonstrated in these trials and did not differ significantly between O3FAs and placebo groups within each trial. The most reported side effects were mild and self-limiting. They included nausea, vomiting, increased stool frequency, dizziness, fatigue, and insomnia.

The safety of probiotics has been established. The theoretical risks include infection, adverse metabolic activities, excessive immune stimulation, and gene transfer in susceptible immunocompromised individuals. As far as strains specific to the investigational products, no safety concerns nor adverse effects were observed in clinical trials administering *Lactobacillus salivarius* CECT5713 (36).

No safety concerns have been reported in studies administering *Lactobacillus paracasei* LC01 (37), *Bifidobacterium animalis* subsp. *lactis* (38), and *Bifidobacterium bifidum* (39) to healthy adults.

Long-term safety and efficacy of probiotics administered during the perinatal period were established in a randomized double-blind placebo-controlled study of over 300 pregnant women involving the following strains: *Lactobacillus rhamnosus* GG, *Bifidobacterium lactis* Bb-12, *Lactobacillus paracasei* ST11, and *Bifidobacterium longum* BL999 (40). The authors found no differences in growth or noncommunicable disease prevalence between children receiving perinatal probiotics or placebo.

The safety profile of probiotics is deemed excellent in healthy adults, and pregnancy is not considered a contraindication for their use.

#### Criteria for study withdrawal

All eligible participants will be informed that their participation is completely voluntary, and they can discontinue participation at any time. Participants may withdraw from the study entirely or from specific parts of the study only. If the latter is desired, then follow-up pertaining to other consented components of the study will continue.

Data collected prior to withdrawal may be retained and used in a manner consistent with the study purpose and protocol. The exception is if participants explicitly request the removal of all previously collected information and data, in which case the study team will oblige. Once a participant expresses a desire to withdraw from the study, the research team member in contact with the participant will confirm whether previously collected data can be retained (or should be destroyed) and whether the participant can be contacted in the future for other research opportunities.

The participant will be notified during consent and at the time of withdrawal that any data retained for the analysis cannot be withdrawn after study closure or publication of the study (whichever comes first). Lost to follow-up is defined as enrolled participants that were randomized and completed all parts of visit 1, but completed zero parts of any subsequent visits (2, 4–7). Five attempts will be made to reschedule the study visits for these participants. The number of attempts and modes of communication to reach these participants will be documented. If the missed study visit is not successfully rescheduled within 4 weeks, the visits will be marked as lost to follow-up. Should the participant return to completing the later visits, they will be included in all analyses consistent with the intention to treat. However, if all attempts to reconnect by the study team fail for the missed visit and all remaining visits, and/or if the participant explain that they wish to stop participating in the study, they will be marked as study withdrawal.

All adverse events during the study period will be recorded, and these records will be maintained for 15 years. The clinical trial sponsor will inform the Natural and Nonprescription Health Product Directorate of Health Canada of any serious expected or unexpected adverse events related to the study product immediately if possible and no later than 7 days after becoming aware of the information. Reported symptoms of psychosis (hallucinations, delusions, or disordered thinking) will trigger a referral of participants to the study psychiatrist for assessment and to determine whether they meet the criteria for withdrawal. If a participant reports a significant worsening in symptoms of anxiety or depression, they will be permitted to remain enrolled in the study but will be advised to contact their primary mental healthcare provider for assessment and management. If the mental healthcare provider suggests that psychiatric rescue medication is needed, this clinician will recommend the treatment to the participant. Changes to treatment regimens must be reported to the study team for documentation.

Serious adverse events will also be reported to the research ethics boards that have reviewed the study protocol.

Participants who complete all parts of the study but fail to adhere to regular supplemental intake (defined as missing 7 or more consecutive days), will be included in the study for as long as they wish. Their reasons for not taking the supplements will be documented, and strategies to help overcome this (i.e., forgetfulness) will be made. If the reasons for stopping supplements are allergic reactions or side effects, they will be withdrawn from the intervention, and an adverse report will be made consistent with the safety protocol. If participants still wish to continue with the study, they may do so as part of the control arm.

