#### Outcomes measured

As a feasibility study, process evaluation will be our primary outcome. In the first 6 months of the trial, we will monitor the number of patients screened, randomized, and enrolled per month; the average time lapse between screening and enrollment; and the time taken to enroll 15% of our target (i.e., *n* = 15). We will also assess baseline rates of O3FA and probiotics supplementation in this specific cohort prior to randomization. We will identify and document all barriers to meeting the target numbers needed for each study arm and address them appropriately. In patients successfully enrolled, we will also monitor compliance, side effects, and challenges in taking supplements in the intervention groups. We will closely document all issues in adhering to intake instructions and attempt to resolve them on a case-by-case basis (i.e., if forgetfulness is a cause, daily automatic email reminders will be sent to that individual). In Gutopia, attaining a daily fiber target of 35 g/day will be monitored frequently via phone call in the first 6 months or until the patient no longer needs the support. Finally, we will assess retention rates, the proportion of study visits completed, and challenges related to the collection and shipment of stool samples, as well as the completion of questionnaires and dietary recall. All barriers to the timely completion of these tasks will be documented and managed on a case-by-case basis. Strategies to overcome each of these barriers will be proposed in the final write-up of this study.

As part of our secondary aims, we will seek the opportunity to produce preliminary data on the association between maternal microbial response to each intervention and self-reported scores on questionnaires of mental health challenges. This will be for exploratory purposes to identify any signals that will further support the conduct of a larger trial.

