#### Data management

The collection and storage of data will be done according to Good Clinical Practice Guidelines. All study staff involved in the collection or entry of data will be trained by the trial coordinator and will complete ethical conduct of research training (Tri-Council Policy Statement: Ethical Conduct of Research Involving Humans 2). Data from potential and enrolled participants will be stored in the secure platform, Research Electronic Data Capture (REDCap), and a password-protected database on a secure server managed by the Canadian College of Naturopathic Medicine. Data collected at each study visit will be captured using an electronic case report form, which will be entered into the database. Questionnaire completion will be done by the study participants through REDCap. Laboratory data will be entered into the database and double-checked for accuracy by a team member blind to participant allocation. An audit of the data will be completed by a senior member of the research team in 3 months. All information obtained during the trial will be kept in a locked cabinet or on a password-protected computer and destroyed (deleted or shredded) after 15 years.

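### The promise to remove all data on request makes no exception for adverse-event records, which the protocol also promises to keep for 15 years

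*Protocol article*

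**What the plan says.** All quotations are from the protocol article.

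**Removal of data** (Criteria for study withdrawal). The default is retention: "Data collected prior to withdrawal may be retained and used in a manner consistent with the study purpose and protocol". Then comes the carve-out: "The exception is if participants explicitly request the removal of all previously collected information and data, in which case the study team will oblige". When a participant says that she wants to withdraw, the staff member in contact with her "will confirm whether previously collected data can be retained (or should be destroyed"). The one stated limit is in time: "any data retained for the analysis cannot be withdrawn after study closure or publication of the study (whichever comes first"). No category of record is exempted.

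**A second route to withdrawal** (same section). A participant is also marked as withdrawn "if all attempts to reconnect by the study team fail for the missed visit and all remaining visits".

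**Retention of records.** Later in the same section: "All adverse events during the study period will be recorded, and these records will be maintained for 15 years". Under Data management, with the period given in years: "All information obtained during the trial will be kept in a locked cabinet or on a password-protected computer and destroyed (deleted or shredded) after 15". Neither sentence refers to removal requests.

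**Outcomes** (Outcomes measured). Process evaluation is the primary outcome. It includes compliance, side effects and difficulties with the supplements in the intervention groups, and also: "Finally, we will assess retention rates, the proportion of study visits completed".

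**The concern.** Two unqualified promises cover the same records. Anyone who asks for removal has by definition withdrawn, so whatever is deleted comes only from women who left. If some left because of side effects, the deletion depends on the outcome being measured. Control women take no study product, so any product-related loss would fall on the intervention arms alone.

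Two things are at stake. One is a complete safety record for products given in pregnancy. The other is an unbiased reading of side effects, and possibly of retention, in a trial whose purpose is to judge whether a larger one is feasible. The article also plans to go on enrolling for efficacy if this stage succeeds.

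**Working it through.** **1. Can both rules be followed?** Take a woman who has an adverse event during follow-up, leaves the study before closure and explicitly asks for removal.

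- The removal rule covers everything collected so far, and her adverse-event record is part of that. It must go.
- The adverse-event rule covers all adverse events in the study period. Her record must stay for 15 years.
- The Data management rule covers all trial information. It must stay for 15 years.
- The closure or publication cut-off does not help, because she asks before either.

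One stated rule has to be broken. Nothing in the article says which gives way.

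**2. What would literal removal do to the outcomes?** The plan states no dropout, removal or side-effect rate, so there is no figure of its own to reproduce. The Discussion gives 75 intervention and 25 control women, 75 + 25 = 100, which agrees with the stated total. Every other count below is an assumption chosen to show direction and range.

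*Retention.* Let N be the number enrolled, W the number who withdraw, and k the number of withdrawers erased from the count altogether. True retention is (N − W)/N. Apparent retention is (N − W)/(N − k). With N = 100:

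| W | True | Apparent, by k erased |
|---|---|---|
| 10 | 90.0% | k = 2: 90/98 = 91.8%; k = 5: 90/95 = 94.7%; k = 10: 90/90 = 100% |
| 20 | 80.0% | k = 5: 80/95 = 84.2%; k = 10: 80/90 = 88.9%; k = 20: 80/80 = 100% |
| 30 | 70.0% | k = 8: 70/92 = 76.1%; k = 15: 70/85 = 82.4%; k = 30: 70/70 = 100% |

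With k = 0, apparent equals true. The same holds for any k if a coded count of enrolled and withdrawn women is kept.

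*Side effects.* Let A of the 75 intervention women have a side effect, and let k of those A be erased. The true rate is A/75. If the woman leaves the count entirely, the apparent rate is (A − k)/(75 − k). If she stays in the enrolment count but her adverse-event record is gone, it is (A − k)/75. With A = 15 (true 20.0%):

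| k | Woman erased | Only her event record erased |
|---|---|---|
| 0 | 15/75 = 20.0% | 15/75 = 20.0% |
| 2 | 13/73 = 17.8% | 13/75 = 17.3% |
| 4 | 11/71 = 15.5% | 11/75 = 14.7% |
| 8 | 7/67 = 10.4% | 7/75 = 9.3% |

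So a surviving head-count protects retention but not the side-effect rate. The side-effect rate is protected only if the adverse-event record itself survives.

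**The case against.** The strongest reply is that the text can be read sensibly as it stands. A specific safety-record rule can be taken to limit a general data-removal rule. Serious product-related events go to Health Canada within 7 days and serious events go to the ethics boards, and deleting the study file does not undo those reports. The article is condensed; the consent form and the separate safety protocol are not shown, and two ethics boards reviewed the study. A right to ask for removal is legitimate in itself.

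Part of this stands. The right to removal is not the defect, and external reports of serious events would survive. However, non-serious side effects have no such second copy in the text shown. The reading in which the safety rule prevails has to be supplied by the reader, because the removal sentence says everything and names no exception. This is a clash between stated rules, not a detail left out for brevity.

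Three stronger readings are tempting but not supported:

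- **Every withdrawing woman is asked whether to destroy her data.** Only those who express a wish to withdraw are asked. Women who cannot be reached are also marked as withdrawn, and nobody can put the question to them. Retention is already the default, so the confirmation step is a consent check that does not reverse it.
- **Dropouts vanish from the retention outcome.** The article does not say so. Removal covers what was previously collected, whereas the withdrawal mark is made at withdrawal, and monthly enrolment counts are kept separately in the first 6 months. Loss from the denominator is possible, because no disposition record is protected, but it is not stated.
- **Stopping supplements for side effects leads to erasure.** A woman who stops for that reason is withdrawn from the intervention and may stay in the study. The data question arises only if she also wishes to leave the study.

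**Conclusion.** The contradiction holds on the text: unlimited removal on request before closure or publication cannot be reconciled with unlimited 15-year retention of adverse-event records, or of all trial information. It affects any woman who has an adverse event, leaves and asks for removal. If the removal rule is followed as written, side-effect rates in the intervention arms are understated. Retention is overstated only if, in addition, no disposition count is kept.

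The size of either bias cannot be computed from the document. It is zero if nobody asks for removal, and the figures above rest wholly on assumed counts apart from the 75 and the 100. The point should be corrected because it bears on primary process outcomes and on the safety record, and because records destroyed in the meantime cannot be recovered.

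**What to change.** Reconcile Criteria for study withdrawal with Data management, and state the result in both the protocol and the consent form:

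- A removal request does not extend to adverse-event records, nor to a minimal coded disposition record: arm, how she was allocated (randomized or assigned), enrolment and withdrawal dates, reason if given, and visits completed.
- Women who ask for removal stay in the denominators for retention and side effects.
- The number of removal requests is reported by arm.

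The question whether to retain or destroy may stay; the exemption alone resolves the conflict.

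The cost is a wording change to the protocol and consent form, approved by the two ethics boards. The one real downside is that a participant can no longer have every trace of her participation removed, so she must be told this at consent.

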## Methods

### Trial design and setting

This is a single-centered, partially randomized placebo-controlled double-blind feasibility trial with three intervention arms (Gutopia, Gutboost, and Gutless) and one active control. In total, 100 pregnant women with a history of depression and/or anxiety/PDA attending Sunnybrook Hospital Clinics in the Greater Toronto Area will be recruited.

Participants in Gutopia will receive a daily dose of both investigational products and dietary counseling on increasing dietary fiber. Participants in Gutboost will receive a daily dose of both investigational supplements, while participants in the Gutless arm will receive fish oil and a placebo. Participants in Gutless and Gutboost will be blinded to the status of the placebo/probiotic they will be receiving. The study member interacting with the patients will also be blinded to the treatment group the participant is assigned to. Participants who fully consent to receiving both investigational products, including placebo, will be fully randomized to one of the intervention arms. Participants not willing or able to take a placebo or probiotics will be assigned (not randomized) to the appropriate group that accommodates their preferences/needs. Participants unable or unwilling to take any of our investigational products will be assigned to the active control arm. Women in the control arm will receive standard care offered to all obstetric patients seen at the hospital.

The study involves six study visits, all of which can be conducted virtually every 3 months from the time of enrollment (**Figure 1**). The last study visit will happen between 9 and 12 months postpartum. Two of the study visits will occur during pregnancy [enrollment (visit 1) and third trimester (visit 2)], with the remaining occurring at 1, 3, 6, and 9 months postpartum. At all study visits, information on diet, mental health, physical activity, and sleep quality will be collected. Additionally, all participants will provide a stool sample at each visit, using our stool collection kits, which will be shipped to or dropped off at our center.

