#### Statistical analysis

Should the trial succeed and we continue to recruit for a larger trial, the following statistical plan will be used to compare mental health outcomes between the groups: we will use mental health scores as the primary outcome and an intent-to-treat approach for these analyses.

Participants lost to follow-up will be assumed to have lost interest/commitment to the study and will be excluded from the analysis. Those who discontinue treatment will still be included.

Between-group differences for EPDS/GAD-7 scores will be analyzed using analysis of covariance (ANCOVA), with group membership as the independent variable, EPDS/GAD-7 as dependent, and pharmacotherapy, exercise status, and any form of psychotherapy as covariates.

The interaction effect between the O3FA and probiotics model will be analyzed and reported in each model. Alternative models will be used if the assumptions of ANCOVA are violated. If differences are found between groups, appropriate *post-hoc* analyses will be conducted to identify where the differences lie. Within-group differences at each time point will be analyzed using repeated measures ANOVA. Data from each follow-up will be compared to baseline scores. EPDS/GAD-7 scores will be the dependent variables, and follow-up times will be our independent variable.

Each stool sample will undergo shotgun metagenomics for taxonomic and functional output readings. A comprehensive analysis of all findings will be conducted by an experienced bioinformatics expert at Zymo Research. All researchers involved in the stool analysis will be blinded to the type of intervention. The relationship between each intervention and the relationship to EPDS and GAD-7 scores will be analyzed and reported by an experienced bioinformatician.

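### Women who stop supplements for side effects may continue as controls; read literally, this conflicts with the planned intention-to-treat analysis by group

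*Protocol article*

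**What the plan says.** The protocol article, under Criteria for study withdrawal, deals with women who stop the supplements: "If the reasons for stopping supplements are allergic reactions or side effects, they will be withdrawn from the intervention". It goes on: "If participants still wish to continue with the study, they may do so as part of the control arm". The same section invokes intention to treat for women who miss visits and later return: "they will be included in all analyses consistent with the intention to treat".

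The Statistical analysis section, which is conditional on the trial succeeding and recruiting on, says "we will use mental health scores as the primary outcome and an intent-to-treat approach for these analyses". The ANCOVA is specified "with group membership as the independent variable, EPDS/GAD-7 as dependent". On stopping treatment it says only "Those who discontinue treatment will still be included", without naming the arm.

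Trial design and setting describes how the arms are formed. For the intervention arms: "Participants who fully consent to receiving both investigational products, including placebo, will be fully randomized to one of the intervention arms". Women who will not or cannot take placebo or probiotics are placed in a suitable group without randomisation. For the control arm: "Participants unable or unwilling to take any of our investigational products will be assigned to the active control arm".

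**The concern.** Intention to treat fixes a woman's group at allocation. A rule that places her in another arm after an adverse reaction makes group membership depend on an event after treatment began, and the planned model uses group membership as its factor.

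Two things would follow if the rule were applied to the data as written. Women who tolerate the supplements poorly would leave the Gutopia, Gutboost and Gutless groups, which include the only randomised comparison in the design. Women already exposed to fish oil, and possibly probiotic, would also enter a control group meant to be unexposed.

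The comparisons at stake are the between-group EPDS/GAD-7 scores and changes (Mental health outcome), the gut profiles across all four arms at each follow-up (Microbial response to diet and supplementation), and the ANCOVA. Compliance and retention denominators could also be affected if they are tabulated by current arm.

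**Working it through.** **Side-by-side reading**

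1. The withdrawal rule changes the arm in which a woman continues. The analysis rule uses the arm as its factor and promises intention to treat. The sentence on women who discontinue keeps them in the analysis but leaves open in which group.
2. No passage says that the control-arm wording refers only to the visit procedures, or that the starting arm governs the analysis.
3. The control arm is defined as women who cannot or will not take the products. A woman who stopped for intolerance fits that definition, so staff could reasonably recode her.
4. The withdrawal section already allows withdrawal from parts of the study with other follow-up continuing. Follow-up off product therefore needs no change of arm.

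**How many women could move**

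Inputs: 75 intervention and 25 control (Discussion; 75 + 25 = 100, which matches the planned total). The article gives no stopping rate, so the rates s are assumptions. Movers m = 75 × s, rounded up to whole women; share of the resulting control group = m / (25 + m).

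| Assumed s | m | Resulting groups | Share of control group |
|---|---|---|---|
| 5% | 3.75, taken as 4 | 71 / 29 | 4/29 = 14% |
| 10% | 7.5, taken as 8 | 67 / 33 | 8/33 = 24% |
| 20% | 15 | 60 / 40 | 15/40 = 38% |

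With only 1 to 3 movers the share is 1/26 = 4% to 3/28 = 11%.

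**What this could do to a contrast with control**

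Assume no treatment effect, and that women who stop score d SD worse than everyone else, whose mean is 0. Intervention minus control is then:

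- starting arms kept: s × d
- women moved: −m × d / (25 + m)
- shift in favour of the intervention: s × d + m × d / (25 + m)

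At s = 8% (m = 6) and d = 0.5: 0.040 + 6 × 0.5/31 = 0.040 + 0.097 = 0.14 SD.

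At s = 20% (m = 15) and d = 0.5: 0.100 + 15 × 0.5/40 = 0.100 + 0.188 = 0.29 SD.

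Over s from 4% to 20% and d from 0.25 to 0.8, the shift runs from 0.010 + 0.027 = 0.04 SD to 0.160 + 0.300 = 0.46 SD. If women who stop score better than the others, d is negative and the shift reverses.

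**What this could do between two intervention arms**

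Under the same assumptions, removing the women who stop changes each arm's mean by its own s × d. A contrast between arms with stopping rates s1 and s2 therefore moves by (s1 − s2) × d. With 12% against 4% and d = 0.5 that is 0.08 × 0.5 = 0.04 SD. With equal rates and equal d it is zero. This effect is smaller than the one on contrasts with control.

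**The case against.** The best reply is that the sentence sits in a section on withdrawal and describes how a woman may stay in the study. It does not define an analysis set. Controls take no study product and have the same visits and stool samples, so continuing with them may simply mean follow-up off product. The passages would then agree, and the detail of analysis sets is commonly left to an analysis plan that is not shown. That reading is possible. But the article does not state it, and the words that are there name an arm. This is a stated rule that conflicts with the stated analysis, so it is more than missing detail.

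Several other objections stand and limit the point:

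- The intention-to-treat plan is written for a conditional larger trial; the present study's primary outcome is process evaluation. The Microbiome profiling section does say that enrolment would continue into that trial, and the between-group score comparisons under Mental health outcome do not carry that condition.
- A reader might infer that side-effect and compliance rates will look better than they are. The documents do not show this. Reasons for stopping are documented, an adverse report is made, and compliance and side effects are monitored in the intervention groups. A woman who keeps attending is retained in whichever arm she is counted. Only denominators tabulated by current arm would be affected.
- A reader might infer that moved women carry an earlier follow-up clock. They do not: all arms share one schedule, from enrolment and then by trimester and months postpartum.
- Not every woman moved was randomised, and the control arm is wholly non-randomised, so contrasts with it are already open to confounding. The rule adds to that problem; it does not create it.
- The tolerability evidence cited for omega-3 describes mostly mild events, which makes the higher assumed stopping rates less likely.
- If women who stop score worse by the same amount at every visit, comparisons of change from baseline would largely remove the shift. The ANCOVA would not, as its listed covariates do not include the baseline score.

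**Conclusion.** The conflict is real and depends on no assumed figure. Taken literally, the withdrawal rule lets a post-treatment event decide arm membership, and the article nowhere restores the starting arm for analysis. It affects the planned between-group score and microbiome comparisons now, and the intention-to-treat analysis if the study continues into the larger trial.

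Its size is not known. The shares of 14%, 24% and 38% of the control group rest on assumed stopping rates, and the 0.04 to 0.46 SD range also rests on assumed worse scores among women who stop. A reader might conclude that the comparisons are biased in favour of the interventions. That is one possible direction only, because nothing in the documents links intolerance of the supplements to EPDS or GAD-7 scores.

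**What to change.** Reconcile Criteria for study withdrawal with Statistical analysis by replacing the control-arm sentence with wording such as: *These women may continue study visits off study product and are analysed, for all outcomes, in the arm to which they were originally randomised or assigned; off-product status and its date are recorded.* The sentence in Statistical analysis on women who discontinue should name the same arm.

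The rule on when product is stopped is a clinical matter and is not touched. The cost is a sentence in the protocol and analysis plan, and an off-product field with date in REDCap. It is best done before any woman is recoded, since starting arms might otherwise have to be reconstructed.
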